#### Primary outcomes

This study primarily seeks to determine whether the interventions, namely the single ketamine infusion, the reward imagery rt-fMRI NFT, and those two interventions combined compared to the placebo conditions show a therapeutic effect by reducing the proportion of cocaine use days. The primary efficacy value is the proportion of cocaine use days between intervention groups on follow-up visit (t3). This is measured using the timeline follow back for cocaine use, which is a standardised and validated instrument to assess cocaine use [57].

In addition to the treatment outcome, the mechanism of action of the interventions is assessed. Firstly, changes in accumbal glutamate levels in the NAcc on the intervention visit I (t1) before and during the ketamine/placebo infusion and on the following intervention visit II (t2), approximately one week after the ketamine/placebo administration are measured by using ^1^H-MRS. Secondly, the mechanistic effects of the reward imagery rt-fMRI NFT are assessed by measuring its clinically relevant transfer effect, which is defined as the difference in performance on the intervention visit I (t1) and the intervention visit II (t2) measured in the percent signal change in the NFT region by using rt-fMRI.

#### Secondary outcomes

Furthermore, psychological and neurobiological changes that are linked with CUD and might result from both interventions are of interest:Changes in cocaine use measured by laboratory urine analysis of cocaine and cocaine metabolites [58, 59]. on t0 and t3Changes in cocaine craving measured by the Obsessive Compulsive Cocaine Use Scale [60]. (OCCUS) on t0, t2, t3, t4, and t5Changes in severity of CUD by using the OCCUS [60]. on t0, t2, t3, t4, and t5Changes in motivation for change regarding cocaine use behaviour by using a visual analogue scale (VAS) on t0, t1, t2, t3, t4, and t5Changes in reward sensitivity by using the Trait Hedonic Capacity Scale [61] (THC) and Domains of Pleasure Scale (Masselink M, Roekel EV, Heininga VE, Vrijen VE, Oldehinkel AJ: Domains Of Pleasure Scale (DOPS): assessing level and change in pleasure across domains, submitted). (DOPS) on t0, t2, t3, t4, and t5Changes in emotion regulation skills by using the Negative Mood Regulation Expectancies scale [62]. (NMR) on t0 and t4Changes in depressive symptoms by using the Beck Depression Inventory [63]. (BDI) on t0, t2, and t3Changes in stress coping measured by the subscale of the Stress & Coping inventory [64]. on t0, t3, and t5Changes in self-esteem measured by the Rosenberg Self-Esteem Scale [65]. (RSES) on t0, t2, t3, and t5Changes in self-efficacy measured by the questionnaire for self-efficacy, optimism, and pessimism [66]. on t0, t2, t3, and t5Subjective effects of the ketamine/placebo infusion measured by the 5-Dimension Altered State of Consciousness Questionnaire [67] (Reissmann S, Hartmann M, Kist A, Liechti ME, Stocker K: Assessing ketamine’s acute psychoactive properties with an enhanced scale for altered states of consciousness: a repeated-infusions study in a depressed patient, submitted) (5D-ASC) and Hood’s Mysticism Scale [68]. (HMS) after the infusion on t1Vividness of mental imagery measured by the Prospective Imagery Task [69]. (PIT) on t0Individual imaging strategies measured by the Neurofeedback Post Questionnaire [70]. as well as the Neurofeedback in between Questionnaires on t1 and t2Current cocaine craving measured by a VAS during t1 and t2Current affect measured by a VAS during t1 and t2Glutamate changes during a craving-inducing video measured by.^1^H-MRS on t3Changes in plasma BDNF measured by an immunoassay kit pre to post ketamine/placebo infusion on t1Course of real time cocaine use, cocaine craving, affect, and reward sensitivity by using ecological momentary assessment (EMA) [71]. between the first five visits (t0, t1, t2, t3, and t4)

#### Other outcomes of interest

An electrocardiogram (ECG) and a clinical interview will be conducted and evaluated at the screening visit (t0) to ensure mental and physical health. To capture the consumption pattern of cocaine and potentially other psychoactive substances, the Interview for Psychotropic Drug Consumption [72] will be conducted on screening visit (t0), intervention visit I (t1), intervention visit II (t2), follow-up visit (t3), and virtual visit (t4).

On intervention visits I (t1) and II (t2) and the follow-up visit (t3), we are conducting qualitative interviews to assess acute and sustained effects of the interventions on the subjective experience and the predictive value of those effects [73, 74].

#### Safety outcomes

The following outcomes are measured on the screening visit (t0) for safety and eligibility reasons:Vital signs measured by a blood pressure monitorCurrent suicidality by using the suicidality questions of the MINI [75].Blood parameters by using routine laboratory analysis

On intervention visit I (t1) vital signs are measured pre and post infusion at four different time points. Individuals of childbearing potential must take a pregnancy test on intervention visit I (t1) and II (t2) before the MR measurement, and all participants must perform a drug urine quick test on both intervention visits before performing any interventions.

On every on-site visit, participants are screened for current suicidality by using the questions from the MINI [75].

### Participant timeline {13}

The schedule for data collection and visits is shown in Table 1. After initial establishment of contact, interested candidates are invited for a screening visit (t0), where the eligibility criteria are checked, and suitable participants are randomly assigned to one of the four study arms. The assigned treatment intervention is performed at intervention visit I (t1) and II (t2). The follow-up visit (t3) assesses first effects of the intervention on behavioural measures. Between each of the first five visits, participants are asked to use an EMA application [71] on their smartphones. To measure long-term effects, there is a virtual visit (t4) and a follow-up survey (t5) scheduled.

### Sample size {14}

Sample size was determined by power analysis (G*Power 3.1) and primarily focused on ^1^H-MRS, the most critical procedure in this project to estimate the required number of participants to detect between- and within-subject effects as well as interaction of those. Prior ^1^H-MRS studies that reported significant glutamate differences with effect sizes measured in psychiatric populations within the striatum showed effect sizes of *d* = 1.6 [76], *d* = 0.89 [12], *d* = 1.93 [77], or measured in other brain regions in tobacco use disorder *d* = 1.03 [78]. Thus, assuming a conservative effect size of *d* = 0.80, an α-error probability of 5%, and a conservative power estimation of 80%, a total sample size of 21 individuals with CUD per group (total sample of 84) would be required to detect a significant group effect between experimental and control groups. Again, assuming an effect size of *d* = 0.80 (*f* = 0.40, respectively) for within-subject comparisons before and after intervention, an α-error probability of 5%, and a conservative power estimation of 80%, indicates that a total number of 111 subjects would be necessary to detect a significant within-factor effect in an ANCOVA model. To account for potential dropout, we will recruit in total 120 participants.

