### Trial design {8}

The trial adopts a randomised, placebo-controlled, double-blind, parallel-group, single-centre design with a superiority framework. The treatment combination among the four arms, each consisting of 30 participants, is depicted in Fig. 1.

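### The figure of 111 behind N=120 does not follow from its stated inputs, 21 per group holds only for an undeclared one-sided test, and the primary efficacy value has no power statement

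*Protocol article*

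**What the plan says.** Protocol article, Sample size {14}, bases the calculation mainly on the spectroscopy measure of glutamate and aims to cover between-subject, within-subject and interaction effects. Two figures follow, both at alpha 5% and power 80%.

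- Between groups, "assuming a conservative effect size of *d* = 0.80", the section concludes that "a total sample size of 21 individuals with CUD per group (total sample of 84) would be required to detect a significant group effect".
- For the same d, converted to f=0.40 and used "for within-subject comparisons before and after intervention", the second calculation "indicates that a total number of 111 subjects would be necessary to detect a significant within-factor effect in an ANCOVA model".

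No separate figure is given for the interaction. The section raises the total to 120 for drop-out. It states neither the sidedness of the test nor the numerator df.

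Statistical methods {20a} plans a repeated-measures ANOVA for glutamate at t1, with four treatment groups and two times. It plans an ANCOVA for cocaine use at t3. Under Primary outcomes, "The primary efficacy value is the proportion of cocaine use days between intervention groups on follow-up visit (t3"). Glutamate change stands under the same heading, as a mechanistic outcome.

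**The concern.** Of the two calculated figures, 111 is the larger and the one from which 120 is reached. A reader who enters the stated inputs into the planned model does not obtain it. Its description also mixes two models, because a within-subject effect belongs to a repeated-measures ANOVA and not to an ANCOVA.

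A reader who applies the usual two-sided convention to the 21 per group will believe that a comparison of two arms has 80% power at that size, which it does not.

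The section also says nothing about what the trial can detect on its central clinical hypothesis. A null result on cocaine use days could then be read as evidence of no effect when the trial could reliably detect only medium to large effects.

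**Working it through.** **Inputs.** d=0.80, f=0.40, alpha 0.05 and power 0.80 come from Sample size {14}. Four equal arms come from Trial design {8}. The four-group by two-time glutamate model comes from Statistical methods {20a}. Sidedness is not stated, so both are tried.

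**1. The 21 per group.** For a two-sample t-test with n per group, the noncentrality is δ = d√(n/2) on 2n−2 df.

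| n per group | δ | Test | Power |
|---|---|---|---|
| 20 | 2.530 | one-sided | 79.9% |
| 21 | 2.592 | one-sided | 81.7% |
| 21 | 2.592 | two-sided | 71.6% |
| 25 | 2.828 | two-sided | 79.1% |
| 26 | 2.884 | two-sided | 80.7% |
| 30 | 3.098 | two-sided | 86.1% |

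The stated 21 is reproduced exactly as the one-sided answer. The two-sided answer is 26 per group, or 4 × 26 = 104.

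For the four-group F-test with 3 df, the noncentrality is λ = f²N. At N=84, λ = 0.16 × 84 = 13.44 on 3 and 80 df, and power is 86.5%.

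**2. The 111.** For the ANCOVA F-test with four groups, λ = 0.16N and the denominator df are N−4, less one per covariate. The smallest N with at least 80% power is:

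| Numerator df | N |
|---|---|
| 1 | 52 |
| 3 | 73 |
| 6 | 92 |
| 9 | 107 |
| 10 | 111 |
| 11 | 115 |

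At 10 df, power is 80.3% for N=111 and 79.8% for N=110. Adding one to four covariates leaves the entries for 1, 3 and 10 df unchanged. In the planned model, time has 2−1 = 1 df, group has 4−1 = 3, and group-by-time has 3 × 1 = 3. No effect has 10.

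**3. A calculation that matches the planned model.** For repeated measures with m=2 times and correlation ρ between them, λ = f²Nm/(1−ρ) on N−4 denominator df. The correlation is not given, so a range is shown.

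| Effect | ρ=0 | ρ=0.5 | ρ=0.9 |
|---|---|---|---|
| Time (1 df) | 27 | 15 | 7 |
| Group-by-time (3 df) | 39 | 22 | 9 |

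For example, at ρ=0.5, λ = 0.16 × 2N/0.5 = 0.64N, which gives 9.6 at N=15 and 14.08 at N=22. If f is instead defined so that it already absorbs the correlation, the requirements are 52 and 73. Neither convention gives 111.

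**4. Cocaine use days.** The document gives no effect size or standard deviation for this outcome, so only standardised effects can be stated. Solving the two-sided t-test for d at 80% power and N=120 gives:

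- ketamine or neurofeedback main effect, 60 v 60: d = 0.52;
- one arm v another, 30 v 30: d = 0.74, before any multiplicity correction.

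**The case against.** The strongest reply is that none of this leaves the trial short for the outcome it was sized on. That stands. The 120 recruited exceeds the two-sided pairwise need of 104, and 111 is larger than any planned glutamate effect requires. For glutamate the error is on the safe side.

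A reader might infer that 21 per group is an arithmetic error, or that the stated 80% power is not delivered. The documents do not support that. The figure is exact for a one-sided test, two-sided testing is never claimed, and the trial is described as having a "single-centre design with a superiority framework". The figure is also enough on the planned 3-df F-test (86.5% at 84), taking f=0.40 as the protocol converts it. The shortfall to 71.6% arises only for a two-sided arm-v-arm comparison at 84, and the trial does not recruit 84. What remains is that the test is under-specified and is not the planned non-directional one.

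A reader might also infer that powering on glutamate was concealed or improper. It is disclosed, and glutamate is listed among the primary outcomes. What remains is that the variable named as the primary efficacy value has no power statement.

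Lastly, the step from 111 to 120 is only 9/120 = 7.5%, which might look too small an allowance for drop-out. The section on non-adherence and missing data {20c} provides for replacing drop-outs before the primary efficacy assessment, so that criticism is not pressed.

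**Conclusion.** The concern holds in three limited parts. First, 111 is wrong as written: at f=0.40, alpha 5% and 80% power it requires 10 numerator df, against 1 or 3 in the planned model, and it is attributed to a model without a within-subject factor. Second, 21 per group is right only for an undeclared one-sided t-test; the two-sided figure for two arms is 26 (104 in total). Third, no figure addresses the proportion of cocaine use days.

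The results use exact noncentral t and F distributions and equal arms. The repeated-measures range also depends on the assumed correlation and on how f is defined. The sample size itself is not in doubt for glutamate at d=0.80. The point is one that should be fixed in the justification, not a flaw that undermines the trial.

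**What to change.** Keep N=120 and rewrite Sample size {14}:

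- Delete 111 as the basis for N, or replace it with a repeated-measures calculation for the model in Statistical methods {20a}. State the numerator df, the assumed correlation and the definition of f. With f=0.40 and correlation 0.5, this gives 15 for time and 22 for group-by-time. The ANCOVA-formula figures of 52 and 73 should not simply be put in its place without saying which definition of f they rest on.
- Restate the pairwise figure as 26 per group (104), two-sided, or declare the test one-sided.
- Justify 120 by the two-sided pairwise power it gives at d=0.80, which is 86.1% for 30 v 30.
- Add the standardised effect on cocaine use days detectable at 80% power, two-sided: about 0.52 for a main effect and 0.74 for arm v arm, before multiplicity correction.

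The cost is text only, with no change to conduct or recruitment. The downside is that the pairwise requirement looks less favourable and the limits on the clinical endpoint become explicit.

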### Recruitment {15}

Recruiting takes place throughout the study timeline. Participants are recruited through different channels, for instance, from the Centre for Addictive Disorders, Psychiatric University Hospital Zurich, University of Zurich, and other clinical institutions specialised in the treatment of SUD. Furthermore, we advertise the study via flyers, advertisements, and on social media (e.g. Instagram, Facebook). Interested persons can also register on the study website, which was specially set up for the study, and are then contacted by telephone by an investigator. During the first telephone contact, potential candidates are pre-screened regarding inclusion and exclusion criteria. Those who pass the telephone screening are invited to the screening visit (t0).

## Assignment of interventions: allocation

### Sequence generation {16a}

Each participant gets a subject code, which is generated by the investigator at study inclusion and is individually allocated. The randomisation of the four study arms is counter-balanced with a 1:1:1:1 allocation ratio as per a computer-generated randomisation schedule using the method of minimisation, with age, gender, and severity of CUD based on the assessment of the DSM-5 criteria by the structural interview MINI [75] at the screening visit (t0) (mild and moderate vs. severe) as binary minimisation variables.

### Concealment mechanism {16b}

Each participant is randomly assigned to one of the four treatment arms. To ensure comparable sample size and sample characteristics in the four treatment arms, a stratified randomisation is performed by first grouping each participant into a stratum based on age, gender, and severity of CUD. The treatment allocation is performed automatically by the data management system, where the allocation list is stored by a person who is not involved in the study procedures and has no interaction with participants. Before study completion, all members of the study team who conduct study procedures with participants are blinded and have no access to the allocation list in the data management system.

### Implementation {16c}

As soon as a participant is found eligible for study participation, the data management system sends an automatic email to the Medical Centre Pharmacy of the Psychiatric Hospital Zurich informing them about the pharmacological treatment, i.e. ketamine or placebo. Since the Medical Centre Pharmacy prepares the infusion according to the treatment allocation in the received email, they are the only members of the study team who know of the pharmacological intervention. However, the staff of the Medical Centre Pharmacy never interacts with participants. The infusion bag will be of identical appearance, including colour, shape, size, and texture.

A second email is sent by the data management system to the investigators of the study team with an allocation code for the reward imagery rt-fMRI NFT. Specifically, the code names “cat” and “dog” correspond each to a different anatomical mask that is used either for the real rt-fMRI NFT or the sham NFT, which will be used for the NFT software program OpenNFT [56] to specify the correct region for the feedback calculation. This allows the investigators to implement the reward imagery rt-fMRI NFT according to the correct NFT allocation without knowing whether it is the real rt-fMRI NFT or the sham NFT. The codes for the reward imagery rt-fMRI NFT allocation have been assigned by a person who is not involved in the study procedures and has no interaction with participants.

## Assignment of interventions: blinding

### Who will be blinded {17a}

The participants, investigators, and the sponsor-investigator are masked to treatment allocation during the entire study duration. To guarantee masking throughout the study, the treatment allocation is kept in a confidential key-locked place on-site and is only accessible by a staff member of the Psychiatric University Hospital Zurich not involved in the study.

### Procedure for unblinding if needed {17b}

In circumstances under which unblinding is permissible, e.g. in case of a medical emergency, an Emergency Code Break in sealed envelopes is available to the investigators. This Code Break should be opened only in emergencies when the identity of the investigational product must be known by the investigator to provide appropriate medical treatment.

## Data collection and management

### Plans for assessment and collection of outcomes {18a}

The study team monitors data in real time to ensure complete data collection for all participants, including those who discontinue treatment. Relevant data from the participant, such as eligibility criteria, demographics, height, weight, vitals, MINI [79], concomitant medications, interview for psychotropic drug consumption, and different questionnaires (see specific information in Table 1) are entered directly by the participant or investigator into the data management system at each visit. Additionally, any data that cannot directly be entered into the system is manually added by trained study personnel and verified through a double-check process. The investigators must maintain source documents for each participant in the study, consisting of demographic information, medical and psychological screening, for example, ECG assessments, laboratory tests, and the original signed informed consent form. All original paper–pencil based data and source data documents are stored in a physical participant folder, and a copy is stored electronically on the password-protected study servers provided by the Psychiatric University Hospital Zurich. Also, the collected ^1^H-MRS and reward imagery rt-fMRI NFT data for each visit are stored on the study server. Data which is collected with the EMA application is stored in an instance of Google’s cloud-based Firestore database in an anonymised fashion [71]. In addition, a backup copy of the EMA data is saved on the study server.

For collecting the data, only standardised questionnaires and tested procedures are used.

### Plans to promote participant retention and complete follow-up {18b}

A participant is considered lost to follow-up if one fails to return for one study visit and is no longer available for upcoming visits or the study staff is unable to contact the participant after at least five attempts. Furthermore, the study team is required to document all attempts to obtain follow-up data.

### Data management {19}

Data management is carried out according to Good Clinical Practice (GCP). A secure data management system (REDCap) is used to collect and manage the collected data, such as questionnaires. Furthermore, a password-protected study server provided by the Psychiatric University Hospital Zurich is used as storage for ^1^H-MRS and reward imagery rt-fMRI NFT data. A detailed description of the data management procedure is found in chapter 18a (plans for assessment and collection of outcomes).

### Confidentiality {27}

All personally identifying information and health information, which is needed for recruitment, participation, and tracking, is securely stored by project personnel on a secured server with limited access. Only trained and delegated study personnel have access to those files and systems. Data entry is only performed by persons authorised to have access. All participant folders with paper–pencil data are kept in a locked file cabinet located behind two locked doors, accessible only to necessary staff.

The dataset does not contain any personally identifying information. Each participant receives a unique study ID number, and the collected data is associated only with this specific number.

### Plans for collection, laboratory evaluation and storage of biological specimens for genetic or molecular analysis in this trial/future use {33}

Urine samples are collected from each participant on the screening visit (t0), intervention visit I and II (t1 and t2), and follow-up visit (t3). Blood samples are collected to screen for participants’ health during the screening visit (t0). Further, two blood samples for the BDNF analysis during intervention visit I (t1) are collected.

All results of the urine and blood analysis are done by the in-house laboratory. The urine and blood samples are disposed of as per policy guidelines by the in-house laboratory immediately after analysis.

Results of the urine and blood analysis are entered by the study team into the data management system and the source data is stored in the physical participant folder. Furthermore, the blood sample for the BDNF analysis obtained during intervention visit I (t1) are being properly prepared and stored in a freezer at −80 °C. These samples are kept under these conditions until the study is completed, at which point they will be analysed by the in-house research laboratory. Only samples of participants, who signed the separate consent form for the further assessment of biomarkers in blood plasma samples, are taken and stored after the planned BDNF analysis for further analysis.

